## 2. Final study protocol and statistical analysis plan

### 2.1 Trial design

This was a prospective double-blind randomized crossover study designed to compare the acute effect of unilateral STN and GPi stimulation on motor symptoms in several patients with PD. Participants with advanced PD who had previously undergone combined unilateral STN and contralateral GPi DBS were screened based on the inclusion and exclusion criteria. Following recruitment, participants were comprehensively evaluated under four randomized, double-blind conditions: (1) Med−STN+GPi−, (2) Med−STN−GPi+, (3) Med+STN+GPi−, and (4) Med+STN−GPi+. The symbol + means on, while − means off. The **intervention** section explains the details of these conditions. All participants and trained assessors were blinded to the conditions, and patients were randomly assessed over the course of two continuous days. (**Figure. 1**)

[figure not shown]

Figure. 1 Trial design.

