### 2.2 Patients

Participants were recruited from the Department of Functional Neurosurgery at Ruijin Hospital, Shanghai Jiao Tong University School of Medicine (Shanghai, China). A total of 10 patients with PD underwent combined unilateral STN and contralateral GPi DBS from September 2017 to September 2018. Following recruitment in April 2020 and screening, eight patients who had received the surgery for 2 to 3 years were included in this study. The inclusion criteria were: 1) diagnosis of idiopathic PD; 2) age between 55 and 75 years, both male and female; 3) treatment with combined unilateral STN and contralateral GPi DBS for 2 to 3 years and with optimal parameters for 3 months; and 4) a Hoehn-Yahr (H-Y) stage of less than 4 in the medication-off state. The exclusion criteria were: 1) history of serious psychosis; 2) history of intractable epilepsy (i.e., seizures); 3) diagnosis of severe cardiac, liver or kidney diseases, or other serious health conditions; 4) dementia (A Mini-Mental State Examination score of <24), inability to comprehend the experimental protocol or voluntarily provide informed consent; 5) lack of cooperation; 6) poorly controlled depression or anxiety. The patients in this study overlapped partly with those in our previous study published in 2020;^5^ those were, patients, 3, 7 and 8. Additionally, according to the asymmetry index, patients were divided into a symmetric group (asymmetry index <0.15, both Med− and Med+ conditions before surgery) and an asymmetric group (asymmetry index ≥0.15, either Med− or Med+ conditions before surgery), and the corresponding subgroup analysis was performed. The asymmetry index was a left-extremity to right-extremity ratio in the MDS UPDRS-III, which was calculated using the formula (left extremity – right extremity) / (left extremity + right extremity). A team of experienced multidisciplinary DBS specialists made the clinical decision regarding the specific DBS target to be used in each patient. That was, unilateral STN DBS was applied to treat the more severe side since we hypothesized that STN is more effective than GPi.

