### 2.4 Randomization and blinding

The testing sequence of the treatment conditions was randomly assigned in a counterbalanced manner on the scheduled days. The order of the DBS conditions was determined by the clinician who randomly picked up one of the eight folded sheets with different conditions written on them (half of the first day GPi; half of the first day STN) but was not allowed to participate in any rating or evaluation. Throughout the study, all participants, raters, and statisticians were blinded to treatment conditions. A movement disorder specialist was responsible for programming. In addition, motor symptom evaluation in this experiment was performed by an experimenter who was blinded to the study protocol and did not participate in data analysis or interpretation. Two raters who were blinded to the conditions conducted the video assessments independently, after which the average rating scores were calculated. For subscores with large deviancy, the final scores were determined after re-evaluation.

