### 2.5 Trial outcomes

Acute turning-on effects of unilateral STN stimulation versus unilateral GPi stimulation on motor symptoms in each patient were compared as the primary outcome. Motor symptoms were defined by the MDS UPDRS-III scores which ranged from 0 to 132, with higher scores indicating more severe motor symptoms. To gain insight into the specific effects of each target, we classified the MDS UPDRS-III subscales into three categories: 1) axial signs, as measured by scores on speech, facial expression, arising from a chair, posture, gait, freezing of gait, and posture stability; scores could range from 0 (no axial signs) to 28 (severe axial signs); 2) STN-stimulated contralateral limb symptoms; and 3) GPi-stimulated contralateral limb symptoms. Limb symptom severity was measured using the subscale scores of the corresponding limb on rigidity, finger tapping, hand movements, hand pronation supination, toe-tapping, leg agility, posture tremor, kinetic tremor, and resting tremor amplitude; scores could range from 0 (no limb symptoms) to 52 (severe limb symptoms). The Berg Balance Scale (BBS) was also compared as a second outcome at the 2- to 3-year follow-up. The patient’s daily dose of antiparkinsonian medication was converted into a levodopa equivalent daily dose (LEDD).

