### 2.6 Data analysis

There were two types of comparisons conducted in this study. The first was the comparison between unilateral STN+ and GPi+ within the same patient group in Med− and Med+ conditions, and the second was the comparison between asymmetric and symmetric groups for the different patient groups in the same condition. Before the comparisons, the Shapiro-Wilk test was used to test the normality of data in each group, yielding the W statistic and *P*-value reflecting the evaluation criteria of distribution. For normally distributed data, a parametric test of the Student’s t-test was used to assess the difference between groups. For the non-normally distributed data, the non-parametric Wilcoxon test was applied to compare the differences. The first comparison mentioned was based on the paired Student’s t-test and Wilcoxon signed-rank test. The second comparison was based on the independent Student’s t-test and Wilcoxon rank-sum test. All three tests mentioned were two-tailed tests with a *P*-value*<0.05* reflective of statistical significance. Statistical calculations and techniques were performed using R-4.0.2.

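### STN was placed against the more severe side by rule, so the unadjusted STN-versus-GPi total-score comparison confounds target with side severity

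*Supplement*

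**What the plan says.** Section 2.2 (Patients) records that a multidisciplinary team "made the clinical decision regarding the specific DBS target to be used in each patient", and gives the rule it followed: "unilateral STN DBS was applied to treat the more severe side since we hypothesized that STN is more effective than GPi". No exception is stated.

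Section 2.4 describes what was randomised: "The testing sequence of the treatment conditions was randomly assigned in a counterbalanced manner on the scheduled days". This is the day order only.

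Section 2.5 sets the main comparison: "Acute turning-on effects of unilateral STN stimulation versus unilateral GPi stimulation on motor symptoms in each patient were compared as the primary outcome". The scale is the whole examination: "Motor symptoms were defined by the MDS UPDRS-III scores which ranged from 0 to 132". It thus includes the limbs on both sides. The same section also defines three categories: axial signs, limbs contralateral to the STN lead, and limbs contralateral to the GPi lead.

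Section 2.6 gives the test: "The first comparison mentioned was based on the paired Student’s t-test and Wilcoxon signed-rank test". No covariate is named. Asymmetry enters only through the symmetric and asymmetric groups (index below 0.15 before surgery in both medication states, or not), which are analysed as subgroups and compared with each other in the same condition. Section 3 says that half of the eight patients met the index criterion.

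Each of the four rated conditions in Section 2.1 has exactly one stimulator on. The one-hour period with both off (Sections 2.3.1 and 2.3.2) has no rating attached.

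**The concern.** In a within-patient crossover each patient is his or her own control, and it is easy to assume that patient characteristics therefore cancel. Side severity does not cancel here, because it is tied to the treatment. On the STN day the worse limbs are stimulated and the better limbs are not; on the GPi day it is the reverse. Randomising the day order protects against period effects, and blinding protects against rating bias, but neither separates the target from the side that it serves.

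At stake is the attribution of the main result. A lower total score on the STN day could reflect the target, the greater room for improvement in the limbs it treats, or both, and the planned test cannot tell these apart.

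**Working it through.** The plan gives no sample-size calculation, effect size or side-specific scores, so there is no figure of its own to reproduce. The size of the problem has to be shown under assumptions.

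**Notation.** W and L are the unstimulated limb scores of the worse and better side, T = W + L, and A = (W - L)/T. A is the magnitude of the index in Section 2.2, taken as worse minus better instead of left minus right. r is the fraction of the contralateral limb score that a target removes, assumed equal for both targets. Ipsilateral effects are set to zero. Values of r and T are assumptions; only the cut-off A = 0.15 comes from the plan.

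**Model 1: equal proportional effect.**
- Limb total, STN day: (1 - r)W + L
- Limb total, GPi day: W + (1 - r)L
- GPi day minus STN day: r(W - L) = r x A x T

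With r = 0.4 and T = 40:

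| A | W | L | STN day | GPi day | Apparent STN advantage |
|---|---|---|---|---|---|
| 0 | 20 | 20 | 32.0 | 32.0 | 0 |
| 0.15 | 23 | 17 | 30.8 | 33.2 | 2.4 |
| 0.30 | 26 | 14 | 29.6 | 34.4 | 4.8 |

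Over r = 0.3 to 0.5, T = 30 to 50 and A = 0 to 0.30, the range is 0 to 0.5 x 0.30 x 50 = 7.5 points.

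**Model 2: equal fixed effect.** If each target removes 8 points whatever the severity, the limb total is 40 - 8 = 32 on both days, and the bias is 0.

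**Effect on the test.** A simulation of the paired t-test used n = 8, two-sided 0.05, T = 30 and assumed A values of 0.03, 0.06, 0.09, 0.12, 0.18, 0.22, 0.28 and 0.35 (mean 0.166). Under Model 1 the mean spurious STN advantage is 1.5 points at r = 0.3 and 2.5 at r = 0.5. The chance of a false finding that STN is better, as the SD of the paired difference falls from 5 to 2 points, is 10% to 36% at r = 0.3 and 20% to 67% at r = 0.5. The nominal rate is 2.5%. Under Model 2, or with the side chosen at random, it stays close to 2.5%.

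**The symmetric subgroup.** At A = 0.15 the side ratio is 1.15/0.85 = 1.35, so the criterion reduces the difference between sides without removing it. The index dates from before surgery, 2 to 3 years before testing. With four patients the smallest two-sided exact signed-rank p-value is 2/2^4 = 0.125.

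**What the limb categories offer.** For the limbs contralateral to one lead, the STN day against the GPi day is that lead on against off. At A = 0.15 under Model 1, the proportional effects are 1 - 13.8/23 = 0.40 for STN and 1 - 10.2/17 = 0.40 for GPi: equal, as they should be. Under Model 2 the same calculation gives 8/23 = 0.35 and 8/17 = 0.47, so this contrast too depends on the scale.

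**Regression on the severity difference.** Under the placement rule the difference (STN side minus GPi side) is zero or positive in every patient, so the intercept lies at or beyond the edge of the data. Relative to the unadjusted mean, its standard error is multiplied by sqrt(1 + n x mean^2/Sxx) at unchanged residual SD. For the A values above this is sqrt(1 + 0.2211/0.0876) = 1.88.

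**The case against.** A reader might infer that the comparison favours STN whenever the targets are equally effective. The documents do not support that. They do not say on what scale efficacy would be equal, and on a fixed-points scale the bias is zero. If the residual scores of the two treated limbs were compared directly, the bias would even run towards GPi: at A = 0.15 above, 13.8 against 10.2.

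A reader might also infer that the plan looks only at the raw total. It does not. Section 2.5 separates axial signs and the limbs contralateral to each lead, and the opposite-target day gives each limb an off reference, although no condition with both stimulators off is rated. Axial signs are not a one-sided limb score, so the r x A x T formula does not reach them. What is missing is a formal comparison of the two limb effects.

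The size is also uncertain. Half of the patients were below 0.15, where A may be close to 0; 2.4 points is the upper limit for that group at the assumed r and T. Limb totals may be lower with medication, and preoperative asymmetry may not describe unstimulated severity at testing.

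All of this stands. It limits the direction and size of the bias, but leaves the confounding of the total-score contrast in place: nothing in Section 2.6 addresses it, and the subgroup split does not remove it.

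**Conclusion.** The point holds. Target and side severity coincide by the rule in Section 2.2, and the unadjusted paired comparison of total MDS UPDRS-III cannot separate them. This follows from the text and needs no numerical assumption.

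The direction does need one: that benefit grows with the severity of the treated side. Given that, and a negligible ipsilateral effect, the bias favours STN by r x A x T. If benefit is a fixed number of points, there is none. The actual size cannot be known from the documents, because they give no side scores.

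The placement itself is not in question here, only what may be concluded from it. It would go too far to say that an observed STN advantage must be spurious, or that the symmetric subgroup carries no information.

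**What to change.** 1. State in Sections 2.5 and 2.6, and wherever results are interpreted, that the total-score contrast is confounded with side severity and compares STN on the worse side with GPi on the better side. Do not conclude from it alone that one target is superior. This costs only wording.

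2. Add a within-patient contrast of proportional effects on each target's own contralateral limbs, by medication state, with its interval:
   - STN: 1 - L_STN(STN+)/L_STN(GPi+)
   - GPi: 1 - L_GPi(GPi+)/L_GPi(STN+)

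   Here L_STN and L_GPi are the limb scores contralateral to each lead. Log ratios are an alternative. State that the contrast assumes little ipsilateral effect of the active lead. State also that it is unstable for small scores (one point is 25% of a reference score of 4 but 5% of 20), and fix in advance how zeros are handled. Show it beside the difference in points, since the two scales can disagree. The data are already collected.

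3. Report a regression of the STN-minus-GPi total difference on the preoperative severity difference at most as a sensitivity analysis, with its interval. With eight patients and severity differences in one direction, the intercept is imprecise and a null result would say little.

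A direct reference with both stimulators off would require retesting, since Section 2 reports the assessments as done. The steps above do not depend on it.

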### 2.3 Interventions

#### 2.3.1 Unilateral DBS of STN

Bilateral stimulation was turned off for an hour^10^, and unilateral STN DBS was turned on afterwards. Participants were asked to complete a comprehensive set of assessments under unilateral STN stimulation in the Med− state. Participants were further required to complete the second set of assessments in the Med+ state one hour after taking regular medications.

#### 2.3.2 Unilateral DBS of GPi

Unilateral GPi DBS was delivered after bilateral stimulation was turned off for an hour. The study protocol was identical to that used in the unilateral STN DBS intervention but was performed on a different day. After all these assessments, bilateral DBS will be turned on again and returned to normal treatment status.

#### 2.3.3 Concomitant interventions

Participants were asked to stop taking antiparkinsonian drugs for 12 h to stay in the Med− state until they completed the first set of assessments. Regular medication was taken one hour before the second set of assessments to maintain a Med+ state. All processes were repeated for the contralateral target on the next day.

### 2.4 Randomization and blinding

The testing sequence of the treatment conditions was randomly assigned in a counterbalanced manner on the scheduled days. The order of the DBS conditions was determined by the clinician who randomly picked up one of the eight folded sheets with different conditions written on them (half of the first day GPi; half of the first day STN) but was not allowed to participate in any rating or evaluation. Throughout the study, all participants, raters, and statisticians were blinded to treatment conditions. A movement disorder specialist was responsible for programming. In addition, motor symptom evaluation in this experiment was performed by an experimenter who was blinded to the study protocol and did not participate in data analysis or interpretation. Two raters who were blinded to the conditions conducted the video assessments independently, after which the average rating scores were calculated. For subscores with large deviancy, the final scores were determined after re-evaluation.

### 2.5 Trial outcomes

Acute turning-on effects of unilateral STN stimulation versus unilateral GPi stimulation on motor symptoms in each patient were compared as the primary outcome. Motor symptoms were defined by the MDS UPDRS-III scores which ranged from 0 to 132, with higher scores indicating more severe motor symptoms. To gain insight into the specific effects of each target, we classified the MDS UPDRS-III subscales into three categories: 1) axial signs, as measured by scores on speech, facial expression, arising from a chair, posture, gait, freezing of gait, and posture stability; scores could range from 0 (no axial signs) to 28 (severe axial signs); 2) STN-stimulated contralateral limb symptoms; and 3) GPi-stimulated contralateral limb symptoms. Limb symptom severity was measured using the subscale scores of the corresponding limb on rigidity, finger tapping, hand movements, hand pronation supination, toe-tapping, leg agility, posture tremor, kinetic tremor, and resting tremor amplitude; scores could range from 0 (no limb symptoms) to 52 (severe limb symptoms). The Berg Balance Scale (BBS) was also compared as a second outcome at the 2- to 3-year follow-up. The patient’s daily dose of antiparkinsonian medication was converted into a levodopa equivalent daily dose (LEDD).

### 2.6 Data analysis

There were two types of comparisons conducted in this study. The first was the comparison between unilateral STN+ and GPi+ within the same patient group in Med− and Med+ conditions, and the second was the comparison between asymmetric and symmetric groups for the different patient groups in the same condition. Before the comparisons, the Shapiro-Wilk test was used to test the normality of data in each group, yielding the W statistic and *P*-value reflecting the evaluation criteria of distribution. For normally distributed data, a parametric test of the Student’s t-test was used to assess the difference between groups. For the non-normally distributed data, the non-parametric Wilcoxon test was applied to compare the differences. The first comparison mentioned was based on the paired Student’s t-test and Wilcoxon signed-rank test. The second comparison was based on the independent Student’s t-test and Wilcoxon rank-sum test. All three tests mentioned were two-tailed tests with a *P*-value*<0.05* reflective of statistical significance. Statistical calculations and techniques were performed using R-4.0.2.

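### The symmetric-versus-asymmetric comparison is set up condition by condition, and no test or confidence interval is planned for whether the within-patient STN-GPi difference depends on asymmetry

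*Supplement*

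**What the plan says.** Section 2.6 (Data analysis) opens with "There were two types of comparisons conducted in this study". The first is within patients: "The first was the comparison between unilateral STN+ and GPi+ within the same patient group in Med− and Med+ conditions". Its tests are paired: "The first comparison mentioned was based on the paired Student’s t-test and Wilcoxon signed-rank test". The second is between patients: "the second was the comparison between asymmetric and symmetric groups for the different patient groups in the same condition". Its tests are unpaired: "The second comparison was based on the independent Student’s t-test and Wilcoxon rank-sum test". All are two-sided at 0.05. No third comparison is listed.

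Section 2.5 (Trial outcomes) names the primary contrast: "Acute turning-on effects of unilateral STN stimulation versus unilateral GPi stimulation on motor symptoms in each patient were compared as the primary outcome". The variable is a score: "Motor symptoms were defined by the MDS UPDRS-III scores which ranged from 0 to 132, with higher scores indicating more severe motor symptoms". Axial and limb subscores and the Berg Balance Scale are likewise defined as scores. No change score and no per-patient STN-GPi difference is defined.

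Section 2.1 lists four assessed conditions, two per medication state, each with exactly one target on. There is no condition with both targets off. Section 2.2 splits the patients at an asymmetry index of 0.15 and announces a subgroup analysis. It adds that the STN lead was assigned to treat the worse side. Section 3 reports 8 patients, half of them below the 0.15 limit, so 4 versus 4.

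**The concern.** The primary contrast is STN against GPi within a patient. A subgroup split by asymmetry therefore naturally raises the question of whether that contrast differs between symmetric and asymmetric patients. This is a group-by-target interaction, and its data are the within-patient differences.

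A between-group test inside one condition is a different quantity. It adds together how severely affected the two groups are and how they respond to that one target. Without a both-off assessment, the two parts cannot be separated within that condition. A significant result could be read as asymmetry altering the merit of a target when the groups merely differ in severity. A true dependence on asymmetry could be missed because between-patient variation has not been removed. The question matters here because the final plan admits asymmetric patients and ties the target to the worse side.

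**Working it through.** The plan states no SD, effect size or power, so there is no figure to reproduce. The check is algebraic, with a simulation for scale.

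**1. What each contrast estimates.** Within one medication state, let D = score(STN+) − score(GPi+) for each patient. On MDS UPDRS-III a negative D favours STN. For group g let m_g be the mean of the two conditions and d_g the mean of D. Then:
- STN+ mean = m_g + d_g/2
- GPi+ mean = m_g − d_g/2

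Write Δ for asymmetric minus symmetric:
- gap in the STN+ condition = Δm + Δd/2
- gap in the GPi+ condition = Δm − Δd/2
- STN+ gap minus GPi+ gap = Δd, the interaction

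Each single gap contains the level difference Δm. Only the difference between the two gaps is free of it.

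**2. Two invented cases, to show the mechanism.**
- Case A: d = −5 in both groups, Δm = 10. Gaps are 10 and 10; the interaction is −5 − (−5) = 0.
- Case B: d = −10 (asymmetric) and 0 (symmetric), Δm = 0. Gaps are −5 and +5; the interaction is −10.

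**3. Simulation.** Assumptions: 20,000 runs per setting, 4 versus 4, normal data, SD 1 in each condition, within-patient correlation ρ of 0.5, 0.7 or 0.9, independent t-tests, two-sided 0.05. None of these SDs or correlations comes from the documents.

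No interaction, severity gap present (ranges are over ρ):

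| Severity gap | Each condition-wise test | At least one of the two targets | Test on D |
|---|---|---|---|
| 1 SD | about 22% | 29–35% | about 5% |
| 2 SD | about 66% | 74–83% | about 5% |
| 3 SD | about 94% | 96–99% | about 5% |

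True interaction, equal average severity:

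| Interaction | Each condition-wise test | At least one of the two targets | Test on D, ρ = 0.5 / 0.7 / 0.9 |
|---|---|---|---|
| 1 SD | about 9% | 17–18% | 23% / 34% / 75% |
| 2 SD | about 22% | 42–43% | 66% / 86% / >99% |

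The second table assumes that the interaction is split evenly over the two conditions. If it fell wholly in one condition, that condition's gap would be the full interaction against an SD of 1, while D has SD √(2(1−ρ)). The test on D would then be stronger only for ρ above 0.5.

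**4. Whether the within-group paired tests fill the gap.** Two P-values set side by side do not test the difference between two effects. With n = 4 the exact two-sided signed-rank P cannot fall below 2/2⁴ = 0.125, so on that branch neither subgroup could ever be significant.

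**5. What the test on D can deliver at 4 versus 4.**
- Smallest exact two-sided permutation or rank-sum P: 2/C(8,4) = 2/70 = 0.029. For the rank-sum test, P < 0.05 requires complete separation of the groups.
- 80% power for a t-test (noncentral t, 6 df) needs a between-group difference of about 2.4 SDs of D.
- 95% CI half-width: t(0.975; 6) × SD_D × √(1/4 + 1/4) = 2.447 × 0.707 × SD_D ≈ 1.73 SDs of D.

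**The case against.** **The tested variable is inferred.** Section 2.6 does not name what the unpaired tests are applied to. Section 2.1 uses the word condition for the four stimulation-by-medication states, but Sections 2.2 and 2.6 also use it for the medication state alone. The second comparison could therefore mean a comparison of STN-GPi differences within one medication state. This is fair. The score reading is likelier because no difference variable is defined anywhere, but it is not certain. The remedy is the same on either reading: the variable must be stated.

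**The contrast is not pure severity.** A reader might infer that the condition-wise tests carry no information on the target effect. The algebra shows otherwise: the two gaps together give the interaction estimate. What is missing is its test and interval. By the same algebra, both true gaps cannot be zero when target effects differ between groups, so non-significant results in that situation reflect low power or chance.

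**Self-control is kept.** A reader might infer that the plan throws away its paired design. It does not: the first comparison is paired and serves the primary question. Pairing is absent only from the between-group comparison.

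**The aim is not stated.** Section 2.2 announces a subgroup analysis without saying that it seeks effect modification. The aim is implied by the primary contrast, so it would go too far to say that the plan fails an objective it set itself.

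**The better test is weak too.** With 4 versus 4 it is close to uninformative unless the effect is very large. This stands, and it is why the result should be an estimate with an interval, labelled exploratory.

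**Conclusion.** The concern holds in this form: on the likeliest reading, the planned between-group tests mix group severity with response to one target, and no test or interval is given for whether the within-patient STN-GPi difference varies with asymmetry. The algebra needs no assumption beyond the score reading. The simulated rates are illustrative only. They depend on assumed normality, SDs, correlations and severity gaps, and nothing in the documents shows that the two groups differ in severity.

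The primary paired comparison is untouched. What is at risk is any conclusion about symmetric against asymmetric patients. Even the corrected contrast will not isolate an effect of asymmetry. STN was assigned to the more severe side, so asymmetry is tied to which target treats the worse limb, and D could differ between groups for that reason alone.

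**What to change.** In Section 2.6, replace the between-group comparison with the following.

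- State the aim: to explore whether the STN-GPi difference varies with asymmetry group.
- For each outcome and medication state, compute D = score(STN+) − score(GPi+) per patient. State the direction of benefit, which is reversed for the Berg Balance Scale.
- Report the between-group difference in D with its 95% CI, and test it once, by t-test or exact permutation test, chosen in the text. If the exact test is used, state the smallest attainable P of 0.029.
- Label the analysis exploratory because of very low power, and do not read a non-significant result as similarity of the groups.
- Note that target and worse limb are tied by the way STN was assigned.
- Present condition-wise between-group scores as description, without P-values, and do not compare subgroup P-values from the paired tests.

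The cost is a rewritten paragraph and a short re-analysis of data already collected. On the score reading, between-group tests per outcome fall from four to two. The price is wide intervals, which show honestly what eight patients can tell.

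If the sponsor in fact tested the within-patient difference, stating the variable and adding the interval and the exploratory label would suffice.

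### For the paired STN versus GPi comparison, normality is screened in each group rather than on the within-patient differences, so an uninformative screen chooses the test

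*Supplement*

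**What the plan says.** The final plan, Section 2.6 (Data analysis), sets out two kinds of comparison: STN stimulation against GPi stimulation within the same patients, separately off and on medication, and asymmetric against symmetric patients in the same condition. Before either, "the Shapiro-Wilk test was used to test the normality of data in each group". Two branches follow: "For normally distributed data, a parametric test of the Student’s t-test was used to assess the difference between groups", and "For the non-normally distributed data, the non-parametric Wilcoxon test was applied to compare the differences".

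The branches are then matched to the designs. For the within-patient contrast, "The first comparison mentioned was based on the paired Student’s t-test and Wilcoxon signed-rank test". For the between-patient contrast, "The second comparison was based on the independent Student’s t-test and Wilcoxon rank-sum test". Tests are two-sided at 0.05. No threshold is given for the Shapiro-Wilk test, and the section does not mention within-patient differences as something to be checked for normality.

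Section 2.5 makes the within-patient STN versus GPi contrast in motor symptoms the primary outcome. On numbers, Section 2.2 says that "eight patients who had received the surgery for 2 to 3 years were included in this study", and the summary of changes in Section 3 says that half of them met the symmetry limit. The subgroups are therefore 4 and 4.

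**The concern.** A paired t-test is a one-sample t-test on the differences. A patient's overall severity enters both conditions and cancels, so the shape of the scores within a condition says little about whether the paired t-test is appropriate. A screen on those scores can reject because a few patients are much more severe than the rest, although the differences are well behaved. It can also pass when severity is bell-shaped and the differences are badly skewed.

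The rule is also incomplete. A paired comparison has two conditions, and the plan does not say which branch applies when one passes and one fails. Two analysts could follow the text on the same data and report different primary p-values.

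The rule is applied many times. The total MDS UPDRS-III score, three subscores and the Berg Balance Scale (Section 2.5), each in two medication states, give 5 × 2 = 10 paired comparisons in the full group. Each may be sent to a different test for reasons unrelated to the STN–GPi contrast.

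**Working it through.** **Inputs from the documents.** n = 8 for the paired comparison (Section 2.2); 4 and 4 in the subgroups (Sections 2.2 and 3); two-sided 0.05 (Section 2.6). The plan gives no SD, effect size or power, so there is no figure of its own to reproduce.

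**Assumptions.** Shapiro-Wilk is run at 0.05. A comparison goes to Wilcoxon if either condition fails. The distributions are mine, since the documents report none.

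**1. Which quantity matters.** Write patient *i*'s scores as X = u + e₁ (STN) and Y = u + e₂ (GPi), where u is the patient's severity. Then D = X − Y = e₁ − e₂, and the paired statistic is t = mean(D) / (s_D / √n). The severity u has dropped out, but it dominates the shape of X and Y.

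**2. Power of Shapiro-Wilk** (20,000 samples per setting):

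| True shape | n = 4 | n = 8 |
|---|---|---|
| Exponential | 12.1% | 33.4% |
| Lognormal | 17.1% | 47.5% |
| t, 3 df | 7.3% | 15.3% |
| Uniform | 6.4% | 7.1% |

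A non-significant screen at these sizes is weak evidence of normality.

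**3. How often each screen rejects at n = 8** (10,000 trials per setting; normal severity has mean 45 and SD 15, skewed severity is lognormal(3.3, 0.8)):

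| Setting | Screen on each group | Screen on differences | The two choose different tests |
|---|---|---|---|
| Skewed severity, normal differences | 38.8% | 5.4% | 39.6% |
| Normal severity, exponential differences | 8.4% | 33.7% | 36.3% |
| Normal severity, heavy-tailed (t, 2 df) variation | 9.5% | 20.7% | 23.9% |
| All normal | 8.7% | 5.0% | 12.9% |

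The per-group screen rejects most often where the paired t-test is sound, and seldom where the differences are skewed.

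**4. Whether the choice changes results at n = 8** (10,000 trials per setting, exact signed-rank test):

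| Setting | Plan's rule | Always paired t | Always signed-rank |
|---|---|---|---|
| Type I error: lognormal(3, 0.8) severity, normal differences (SD 3 per condition) | 0.048 | 0.051 | 0.043 |
| Power: the same, 4-point shift | 0.60 | 0.63 | 0.56 |
| Type I error: differences exponential, centred at zero | 0.105 | 0.107 | 0.085 |
| Power: differences exponential, mean 4 | 0.89 | 0.88 | 1.00 |

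With a 4-point effect, the t-test and the signed-rank test disagree on significance in roughly 10% to 13% of trials. In those trials the branch taken decides the verdict. In the last row every patient differs in the same direction, so the signed-rank test always rejects, and the disagreement is 1.00 − 0.88 = 0.12.

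**5. Smallest attainable two-sided p without ties.** For n pairs, the exact signed-rank and sign-flip tests cannot go below 2/2ⁿ.
- n = 8: 2/256 = 0.0078.
- n = 4: 2/16 = 0.125.
- Rank-sum, 4 against 4: 2/C(8,4) = 2/70 = 0.0286.

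In a paired comparison within four patients, being sent to the exact signed-rank test rules out significance at 0.05, while the t-test could still reach it.

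**The case against.** The strongest reply is that the rule does no measurable damage to error rates. That stands. With normal differences its type I error (0.048) lies between those of the two fixed tests, and so does its power. With skewed mean-zero differences it is too high (0.105), but so is the plain t-test (0.107), so the pre-test is not the cause. The signed-rank test is also above 0.05 there (0.085), because it relies on symmetric differences. A reader might infer from the word pre-test that the significance level is inflated by it; these figures do not support that.

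Second, a reader might take the wrong-quantity criticism to cover all of Section 2.6. It does not. For asymmetric against symmetric patients, normality within each group is what an independent t-test assumes. Only the low power at n = 4 counts against the screen there.

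Third, the word group is ambiguous: the same section also uses it for sets of patients. The plan does not say outright that raw condition scores were screened, but it nowhere says that differences were. The wording needs mending on either reading.

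Fourth, the choice is made by a written rule, and the move away from a fixed signed-rank test is listed openly with a reason. The documents do not support a suggestion of ad hoc choice. The data select the test, but through a stated, if incomplete, procedure.

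**Conclusion.** The point holds for the paired, primary comparison. The plan lets a low-powered screen of the wrong quantity choose the test, and leaves mixed results unresolved. At n = 8 the per-group screen and a screen on the differences lead to different tests in about 13% to 40% of trials, depending on the assumed distributions. With a 4-point effect, the two candidate tests disagree on significance in roughly 10% to 13%.

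The consequence is arbitrary selection that can alter which of the 10 paired results are labelled significant. It does not make the primary result invalid, and no excess of false positives is attributable to the pre-test. All percentages rest on assumed distributions, a 0.05 screening level and the assumption that either failure leads to Wilcoxon. The direction of the argument, that patient severity cancels in the differences, rests on none of these.

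**What to change.** For the paired comparison, delete the Shapiro-Wilk branch. Name one test for every paired comparison in the 8 patients, for example the exact signed-rank test (the test in the original plan) or a sign-flip permutation test on the 8 differences. State how ties and zero differences are handled. Report the mean or Hodges-Lehmann difference with a 95% CI, and give a paired t-test on the differences as a sensitivity analysis. Moving the screen to the differences would not be enough, since it would still miss about two thirds of exponential samples at n = 8.

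Present paired comparisons within the four-patient subgroups descriptively, with estimates and intervals and the interval method named. An exact signed-rank interval there reaches at most 1 − 0.125 = 87.5% coverage, so it cannot be labelled 95%.

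For asymmetric against symmetric patients, likewise name one test, for example the exact rank-sum test, whose smallest two-sided p of 0.0286 leaves significance attainable.

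The cost is a change of wording and a re-run of the tests. If the differences are truly normal, power falls modestly, about 0.56 against 0.63 for the t-test in the assumed scenario.
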